## Abstract

**Background:**

Hearing impairment at the workplace, and the resulting psychosocial problems are a major health problem with substantial costs for employees, companies, and society. Therefore, it is important to develop interventions to support hearing impaired employees. The objective of this article is to describe the design of a randomized controlled trial evaluating the (cost-) effectiveness of a Vocational Enablement Protocol (VEP) compared with usual care.

**Methods/Design:**

Participants will be selected with the 'Hearing and Distress Screener'. The study population will consist of 160 hearing impaired employees. The VEP intervention group will be compared with usual care. The VEP integrated care programme consists of a multidisciplinary assessment of auditory function, work demands, and personal characteristics. The goal of the intervention is to facilitate participation in work. The primary outcome measure of the study is 'need for recovery after work'. Secondary outcome measures are coping with hearing impairment, distress, self-efficacy, psychosocial workload, job control, general health status, sick leave, work productivity, and health care use. Outcome measures will be assessed by questionnaires at baseline, and 3, 6, 9, and 12 months after baseline. The economic evaluation will be performed from both a societal and a company perspective. A process evaluation will also be performed.

**Discussion:**

Interventions addressing occupational difficulties of hearing impaired employees are rare but highly needed. If the VEP integrated care programme proves to be (cost-) effective, the intervention can have an impact on the well-being of hearing impaired employees, and thereby, on the costs for the company as well for the society.

**Trial registration:**

Netherlands Trial Register (NTR): NTR2782

## Background

Hearing impairment is a common chronic condition in The Netherlands and worldwide. Although the vast majority of adults with hearing impairment has already retired [1], there is a considerable number of younger persons with hearing impairment still active in the labor force. The prevalence of hearing impairment in the Dutch labor force is about 3% (255.000 people) [2]. These numbers are comparable with estimations of the global burden of hearing loss according to the World Health Organization (WHO) [3]. It is well established that hearing impairment is age-related [3]. The expectation is that the number of employees with hearing impairment will increase in the near future because of the ageing population, which have a higher prevalence of hearing impairment, together with plans to increase the retirement age. A problem for hearing impaired employees is that occupations nowadays more and more depend on communication skills. As described by Ruben [4], the modern western economics underwent fundamental changes during the second half of the 20th century. While society was largely dependent on manual labor in the past, occupations today rely more on communication abilities. This implies a greater burden on people suffering from hearing impairment. Altogether, this may lead to an increasing number of hearing impaired employees who need help for problems in the workplace situation.

So far, only a few studies have addressed the impact of hearing impairment on work performance. The studies that have been revealed that there is a range of concerns and problems that hearing impaired employees are likely to experience. Most frequently reported issues are lack of control, problematic functioning in environmental noise, concerns about job safety, sick leave, and the fear to loose employment [5-8]. Furthermore, fatigue and distress are considered as effects of hearing impairment arising due to the constant need to adapt to, and to compensate for the hearing impairment [9]. 'Need for recover after work' refers to the degree to which employees are able to recover from fatigue and distress after one day of work [10]. It is an important factor influencing an individual's physical and mental functional status, and thus the ability to cope with work. The model of Job Demand Control (JDC) makes a distinction between different psychosocial work conditions, such as psychological job demands and job control [11]. According to this model need for recovery can be seen as a short term effect of work [10]. A study by Nachtegaal et al. [12] showed significantly higher levels of 'need for recovery after work' among hearing impaired employees (46%), compared to normally hearing colleagues (38%). They also found that for every dB signal-to-noise ratio (dB SNR) poorer hearing test score, the need for recovery after work increased with 1.4 points. Due to these issues, hearing impaired employees are likely to experience problems varying from direct auditory dysfunctioning to more secondary issues such as psychosocial problems.

Hearing impairment has consequences not only for the working hearing impaired individuals themselves, but also for companies and society. Previous studies showed that hearing impaired people are overrepresented in the group taking sick leave from work [13] and that these persons received more health care [14] in comparison with normal hearing colleagues. This results in higher costs for both the company and society. Additionally, Mohr et al. [15] showed that most of the societal costs of hearing impairment are caused by reduced working productivity due to presenteeism (i.e., being present at work but not functioning at full capability).

A search of the literature showed that interventions specifically supporting hearing impaired employees have scarcely been described. Programmes, other than those aimed at preventing noise-induced hearing loss, for example the protocol of the Dutch Board for Occupational Medicine (NVAB) [16], are practically non-existent. It seems that in current audiological practices, the specific needs of hearing impaired people with work-related difficulties are not dealt with in a standard approach. In The Netherlands, usual care to handle with hearing impairment at work consists of the common guidance and (workplace) advices from the occupational physician (OP). The OP can refer the employee to the general practitioner, to the ear nose and throat (ENT) specialist, or to an audiologic clinic for further audiological diagnostics and care [17]. The possible hearing aid fitting is done by a hearing aid dispenser. There is anecdotal evidence indicating that this usual care does not solve all the problems at the workplace that arise from hearing impairment [8]. It is suggested that a timely coordination of multidisciplinary services is required to fully support and facilitate employees with hearing impairment [8,9]. Additionally, it is argued that if not taken care adequately, disabilities in the workplace due to hearing impairment may result in a substantial health problem and productivity loss with substantial costs for the society as a whole. Therefore, interventions in aural rehabilitation specifically focusing on work-related problems for hearing impaired employees are needed to reduce costs.

An integrated care programme to facilitate and improve the working situation for hearing impaired employees was developed by Kramer et al. [18]. The International Classification of Functioning, disability and health (ICF) provided the theoretical framework for this integrated care programme [19]. In this framework, not only the individual's health condition (hearing impairment at the workplace) but also environmental and personal factors play an important role. A hearing impaired person's disability and functioning should be seen as outcomes of interactions between an individual's health condition, activities, participation, environmental factors (room acoustics, detection of sounds, colleagues, task schedules), and personal factors (age, cognitive capacities, coping styles, education). The integrated care programme for hearing impaired employees, the Vocational Enablement Protocol (VEP), addresses all these factors in the ICF model to improve the participation of hearing impaired employees. The VEP integrated care programme consists of a multidisciplinary assessment of auditory function (body structures and functioning), personal characteristics (personal factors), workplace characteristics (environmental factors), and work demands (activities, participation). The main aim of the VEP integrated care programme is to facilitate participation in and retention of work for hearing impaired employees.

Satisfaction and experiences with the VEP integrated care programme is already evaluated and described elsewhere [18]. However, it is not yet known whether this integrated care programme is effective and cost-effective in comparison with usual care. Randomized controlled studies to examine the cost-effectiveness of an intervention are still rare in the field of audiology. This paper describes the design of a randomized controlled trial to evaluate the effectiveness and cost-effectiveness of the VEP integrated care programme compared with usual care in reducing the 'need for recovery after work'.

## Methods/Design

### Study design

A two-armed randomized controlled trial, with a follow-up of one year will be performed. Employees randomly allocated to the intervention group will receive the VEP integrated care programme; employees allocated to the control group will receive usual care. Measurements will take place at baseline, and 3, 6, 9, and 12 months after baseline measurement. The study design is presented as a flow diagram in Figure 1. The study design, as well the measurements and the structure of the VEP integrated care programme are described in the following paragraphs. The study protocol is approved by the Medical Ethics Committee of the VU University Medical Center. Participation is voluntary and all participants will sign an informed consent prior to inclusion.

**Figure 1 F1:**
[figure not shown]
**Study design**.

### Study population

The study population will be recruited from three occupational health services (OHSs) in The Netherlands. One OHS is attached to a university including a university medical hospital. The second is the OHS of an international steel industry company. The third OHS is attached to an airline company. Employees will be invited to participate during organizational periodical health screenings (PHSs) if their pure-tone audiogram shows a hearing impairment (for a definition of hearing impairment see Inclusion and exclusion criteria for the study population), or participants can present themselves after reading a flyer of the study distributed among the employees of the participating companies. Potential participants will be selected on the basis of both measured hearing impairment and the self-rated level of distress (i.e., experience of problems at work). To screen employees for eligibility on these two factors, the 'Hearing and Distress Screener' (HDS) is developed. The HDS contains five items. Table 1 shows the items and the codes assigned to the answer category per item. Items 1 to 3 are obtained from the distress scale of the Four-Dimensional Symptom Questionnaire (4DSQ) [20,21]. A recent study showed that a high score on those questions can be used as a quick screener for distress [22]. Item 4 specifically addresses the individual's hearing ability at work. Item 5a requests employees to perform the 'National Hearing Test' [23,24]; an adaptive speech-in-noise test that uses digit triplets that are presented against a background of masking noise according to an adaptive procedure. The test measures the speech-reception-threshold (SRT) corresponding to 50% intelligibility. The scores of the 'national hearing test' are classified into three categories representing: good (SRT_n _< -5.5 dB), insufficient (-5.5 ≤ SRT_n _≤ -2.8 dB), and poor hearing (SRT_n _> -2.8 dB) [25]. If the participants have a hearing impairment based on regular pure-tone audiogram (for a definition of hearing impairment see Inclusion and exclusion criteria for the study population), the participant scores also 4 points for item 5 (item 5b). The total score on the HDS can range from 0 to 14. A total score of 7 or more is the criterion cut off for study inclusion. This screening method allows researchers to approach hearing impaired employees who experience problems at work. The HDS will be available over the internet.

**Table 1 T1:** Hearing and Distress Screener (HDS); the items, answer categories, and scores per answer category

	No	Sometimes	Regularly
1. During the past time, did you suffer from listlessness?	0	1	2

2. During the past time, did you suffer from worry?	0	1	2

3. During the past time, did you feel tense?	0	1	2

4. Did you suffer from hearing problems at your workplace?	0	4	4

	Good	Insufficient	Poor

5. a. The score of the National hearing Test?	0	4	4

	No	Yes	

b. Or a mean pure-tone hearing loss at 1, 2, and 4 kHz in at least one ear > 25dB hearing loss.	0	4	

#### Inclusion and exclusion criteria for the study population

Inclusion criteria

1. Diagnosis of hearing impairment (i.e., mean pure-tone hearing loss at 1, 2 and 4 kHZ in at

2. least one ear > 25 dB Hearing loss) or a score of 'insufficient' or 'poor' on the National Hearing test

3. A score of ≥ 7 on the 'Hearing and Distress Screener'

4. Age above 18 year

5. Paid work for at least 8 hours a week

6. Able to complete questionnaires in Dutch

7. Available for the study for the following 12 months

Exclusion criteria

1. Tinnitus is the primary condition affecting the individual

2. Already referred to or received the VEP integrated care programme during the past 12 months

3. Not willing or unable to comply with the VEP integrated care programme

4. Employee is pregnant

Employees with a score of 7 or more on the HDS and who indicate to be willing to participate, will be contacted by the researcher by e-mail or telephone. During this contact, the researcher provides information about the implications of participation in the study and sends written information to the employee's home. The researcher then plans a face-to-face appointment with the employee about one week after having sent the written information. During this appointment the inclusion and exclusion criteria will be checked (Inclusion and exclusion criteria for the study population), informed consent will be obtained and the baseline questionnaire will be completed. At the end of the appointment the employee will be randomized to the intervention or control group.

### Randomization and stratification

All eligible participants will be randomly assigned to the intervention or the control group after the baseline measurements. To prevent an unequal distribution among groups, employees will be pre-stratified on two prognostic factors before randomization. The first one is requirement of hearing protection at the workplace. The second prognostic factor is psychosocial related problems based on the HDS (score of 3 or more on the three distress items (items 1 to 3) of the HDS). This results in a total of four strata. Furthermore, block randomization, with blocks of four, will be applied to ensure equal groups sizes within each stratum and for practical reasons. An independent statistician will prepare the randomization schedule by using computer-generated random numbers. The research assistant will arrange sealed envelopes before the start of the study containing either a referral to the intervention group or to the control group. When the baseline questionnaire is completed, the employee can choose an envelope in the correct stratum that contains the randomization under the researcher's supervision.

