### Blinding

Due to the nature of the intervention, it will not be possible to blind the participants, the multidisciplinary team of the VEP integrated care programme, or the OPs of the companies to treatment allocation. After randomization, all participants will receive a non traceable research code consisting of consecutive numbers. A research assistant will enter all data into the computer using these research codes. Thus, the researcher who will analyse the data will be blinded.

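### Letting the employee choose an envelope conflicts with blocks of four: depending on how it is read, either block balance is not ensured or some allocations can be foreseen

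*Protocol article*

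**What the plan says.** All of the following is in the Protocol article.

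- **Randomization and stratification, schedule.** "An independent statistician will prepare the randomization schedule by using computer-generated random numbers". Two prognostic factors are used for stratification: "This results in a total of four strata". Within them, "block randomization, with blocks of four, will be applied to ensure equal groups sizes within each stratum and for practical reasons".
- **Same section, draw.** "The research assistant will arrange sealed envelopes before the start of the study". Once the baseline questionnaire is complete, "the employee can choose an envelope in the correct stratum that contains the randomization", with the researcher supervising.
- **Inclusion and exclusion criteria.** The researcher contacts the employee and plans a face-to-face appointment. "During this appointment the inclusion and exclusion criteria will be checked"; consent and the baseline questionnaire follow, and randomization comes at the end of that appointment. Exclusion criterion 3 concerns willingness and ability to comply with the VEP programme, which is a matter of judgement.
- **Blinding.** Participants, the VEP team and the occupational physicians are not blinded. Participants receive research codes after randomization, from which the article concludes: "Thus, the researcher who will analyse the data will be blinded".

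**The concern.** A permuted-block schedule keeps its promise of equal arms only if each new participant takes the next entry on the list. The section promises equal arms and then describes a draw in which the participant picks. This is not a detail left out of a condensed article: the article states a procedure, and that procedure does not fit the schedule it is meant to deliver.

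What is at stake depends on which envelopes are offered, and the text does not say.

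- **Whole stratum pile offered.** The blocks have no effect and the stated balance is not ensured.
- **Current block only offered.** Balance is kept, but the end of each block can be foreseen by anyone who knows the block size and has seen the earlier draws. Treatment is open and the primary outcome, need for recovery after work, is self-reported. Concealment of the next allocation is therefore the main protection against selection at enrolment, and selection at that point cannot be reliably corrected in the analysis.

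**Working it through.** The article gives no figure for balance or predictability, so there is none to reproduce. Inputs from the article: fixed block size 4, two arms of equal size, four strata, 160 participants. Assumptions: 40 enrolled per stratum (160/4), and piles of 40 to 160 envelopes, half per arm. Neither stratum size nor pile size is stated.

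**Reading A: choice from the whole stratum pile.** With n = 40 draws from M envelopes, the number X allocated to one arm is hypergeometric and the arm difference is 2X − 40. Its SD is

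2 × √[ n × ¼ × (M − n)/(M − 1) ].

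For M = 80: 2 × √(40 × 0.25 × 40/79) = 2 × √5.063 = 4.5.

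| Pile M | SD of arm difference in a stratum | P(difference ≥ 6) |
|---|---|---|
| 40 (exactly used up) | 0 | 0% |
| 60 | 3.7 | 17% |
| 80 | 4.5 | 26% |
| 160 | 5.5 | 36% |

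Blocks of four used in order never let the difference in a stratum exceed 2. Under free choice, the first four draws split 2:2 in only 38–40% of cases (M from 40 to 160), against 100% for a real block.

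Over four strata with M = 80, the SD of the overall difference is 2 × 4.5 = 9.0, and its absolute value has a 95th percentile of 18, i.e. 71 against 89. At the article's effect size of 0.40 and two-sided 0.05, power is Φ(0.40/√(1/n₁ + 1/n₂) − 1.96). This is 71.6% for 80/80 and 71.0% for 71/89, a loss of 0.6 percentage points. (The absolute level of power is a separate matter; only the difference is relevant here.)

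**Reading B: choice within the current block.** There are six equally likely arrangements of two and two. An observer who knows the size and the earlier draws guesses the arm with more places left.

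| Draw in block | P(known with certainty) | P(guess correct) |
|---|---|---|
| 1st | 0 | 1/2 |
| 2nd | 0 | 2/3 |
| 3rd | 1/3 (first two equal) | 1/3 × 1 + 2/3 × 1/2 = 2/3 |
| 4th | 1 | 1 |

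Certain: (1/3 + 1)/4 = 33.3%, about 53 of 160 if all blocks are filled. Correct guesses: (1/2 + 2/3 + 2/3 + 1)/4 = 2.833/4 = 70.8%, against 50% under full concealment.

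**Effect of varying the block size.** This was simulated for strata of 40, with sizes mixed with equal probability and an observer who knows which sizes are in use but not their order.

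| Block sizes | Known with certainty | Best guess correct |
|---|---|---|
| 4 (as planned) | 33.3% | 70.8% |
| 2/4/6 | 4.0% | 69.9% |
| 4/6 | 5.6% | 68.9% |
| 4/6/8 | 2.3% | 67.6% |

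Including blocks of two helps the guesser: a fixed block of two gives 50% certain and 75% guessed correctly.

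**The case against.** The case for leaving this as a wording query has several parts.

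- **The two harms are alternatives.** A reader might infer that the procedure loses both balance and concealment. It does not. Under free choice from the pile there are no block ends to foresee; within the current block, balance is kept. This stands.
- **The imbalance is modest.** It rests on an assumed pile, vanishes if the pile is exactly used up, costs under one percentage point of power in the example, and does not bias the comparison. This stands, so it would be too strong to say that balance is destroyed.
- **Predictability is not caused by the choosing.** Numbered envelopes in fixed blocks of four would give the same 33% and 71%. This stands. Both figures are also upper limits: they need a researcher who knows the block size, sees every earlier draw, tracks four strata and acts on it. The article states none of this, although supervising the draw makes seeing earlier allocations the natural reading.
- **There are safeguards.** An independent statistician makes the list, envelopes are sealed before the start, and consent, eligibility and baseline come before the draw. Most entry criteria are objective or scored beforehand. This narrows the room for steering but does not close it: consent and exclusion criterion 3 are settled at the same appointment, and a sealed envelope does not prevent counting within a block.
- **Envelope numbering and opening logs may be in the full protocol.** Agreed; their absence is not the point. The stated choice is.

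A reader might also infer that the analyst cannot be blinded because the researcher watches the draw. That would apply only if the supervising and the analysing researcher are the same person, which the article does not say.

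**Conclusion.** The section contradicts itself: a blocked schedule meant to ensure equal arms within strata is combined with a draw that is not use of that schedule in order. One of two consequences follows, and the text does not settle which.

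- **Whole pile:** balance is not ensured. For 40 draws from 80 envelopes (assumed) the SD of the arm difference is 4.5, against a cap of 2. The cost is a failed promise, with little loss of power and no bias.
- **Current block:** balance holds, but up to 33% of allocations could be known with certainty and up to 71% guessed, before consent and exclusion criterion 3 are settled. This is the more serious consequence. It is conditional on a researcher who knows the fixed block size and has followed the earlier draws.

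The contradiction itself is certain from the text; the sizes depend on the assumptions named. The remark on analyst blinding is secondary and conditional, and adds no weight.

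**What to change.** Amend the section on randomization before the first envelope is opened:

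1. Remove the employee's choice.
2. Open sealed, sequentially numbered envelopes for each stratum strictly in schedule order, and only after consent, eligibility and the baseline questionnaire are complete.
3. Have the independent statistician build the schedule with randomly varying block sizes that are not disclosed to the enrolling researcher, preferably 4/6 or 4/6/8 and without blocks of two.

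Ordered use restores the blocks. Varying the sizes cuts the allocations known with certainty from 33% to about 2–6%. It should not be presented as more than that: the best-guess rate falls only from 71% to about 68–69%, because guessing the lagging arm does not need the block size. Keeping earlier allocations from the enrolling researcher, for example by central allocation, would add protection.

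The cost is a new schedule and renumbered envelopes. Balance within strata becomes slightly less exact: the cap on the arm difference is half the largest block, so it rises from 2 to 3 with blocks up to six, or to 4 with blocks up to eight.

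One sentence should also say whether the researcher who supervises the draw is the one who analyses the data. If so, the claim of analyst blinding should be changed or the analysis given to someone else.
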